**Fig. 1 Fig1:**
[figure not shown]
Schematic representation of the experimental design. TEFDD-c: Continuous Dynamic Stress Test; MAL: Motor Activity Log; NAS: Nottingham Assessment Sensory; WMFT: Wolf Motor Function Test; TECP: Cardiopulmonary Exercise Test; BBT: Box and Block Test; NHPT: Nine-Hole Peg Test; SS-QOL: Assessment of quality of life. AE: Aerobic Exercise; m-CIMT: Modified Constraint-Induced Therapy Movement. T1, T2 and T3 will be performed at 3, 30, and 90 days postintervention

### Randomization and blinding

The randomization method will be matched by age and gender at 1:1 per-muted block randomization generation by a web-based randomization tool (www.random.org). This sequence will be performed independently and remotely by a blinded investigator who will not have contact with other research procedures. Randomization will be concealed until group allocation.

Participants will not be identified by their real names and will not be aware of which study arm they allocated. Thus, the assessors will also be blind, as they will identify the patients by codes and will not have contact with other research procedures. The same standards will be applied to the staff responsible for following the m-CIMT procedures. Data analysis will be conducted by a researcher who is not involved in any stage of recruitment, screening, assessment, or intervention.

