### Sample size

The sample size was calculated with G*Power software using the independent t-test, 85% power, alpha 0.05, and 20% drop-out. Data from the Nine-Hole Peg test proposed by Yoon et al. (2014) [29] were considered for this calculation. Thus, a sample size of 78 individuals (39 per group) is required for this study (Fig. 1). However, after collecting the first five participants per group, the sample size will be recalculated for the same variable.

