### Statistical analysis

Demographic characteristics, such as weight, height and body mass index, will be presented as the mean and standard deviation. Median, maximum and minimum values will be used to describe poststroke time and UE-FMA score.

For all dependent variables, normality (Kolmogorov-Smirnov) and homogeneity (Levene) tests will be applied. If the variables present a normal and homogeneous distribution, then two-way analysis of variance with repeated measurements and Bonferroni’s correction will be used to examine the effect of group-by-evaluation time interaction, group (AE + m-CIMT and Stretching + m-CIMT), and evaluation time (baseline, 3, 30 and 90 days after the intervention). To protect against Type I error, Bonferroni’s correction will be used. Thus, each of the 10 planned comparisons will have to achieve *p* = 0.005 for statistical significance. The partial eta squared (η^2^) will be used to determine the effect size of the intervention. The mean difference from pre- and post-interventions and the corresponding 95% confidence interval (95% CI) will be calculated for each group (EA + m-CIMT and Stretching + m-CIMT) in order to estimate the effect of the intervention.

Otherwise, the Friedman test (*p* < 0.05) will be used followed by the Wilcoxon test with Bonferroni’s adjustment (*p* < 0.008) to compare evaluation time for each group baseline, 3 days, 30 days, 90 days after the end of treatment. The Mann-Whitney test with Bonferroni’s adjustment (*p* < 0.012) will be used to compare the groups in each time evaluation (EA + m-CIMT and Stretching + m-CIMT).

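### Allocation is matched on age and gender but the between-group tests include neither, so those tests are conservative to the extent that the two factors are prognostic

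*Protocol article*

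**What the plan says.** In the protocol article, the section Randomization and blinding restricts the allocation: "The randomization method will be matched by age and gender at 1:1", with permuted blocks drawn up by an online tool.

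The section Statistical analysis then names the terms of the parametric model, which "will be used to examine the effect of group-by-evaluation time interaction, group (AE + m-CIMT and Stretching + m-CIMT), and evaluation time". If normality or homogeneity fails, Friedman and Wilcoxon tests compare times within each group, and a Mann-Whitney test compares the groups at each time. Age and gender appear in neither route. The abstract gives the same methods.

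The thresholds are fixed as well. On the parametric route "each of the 10 planned comparisons will have to achieve" p = 0.005; the Mann-Whitney tests use 0.012.

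The sample size was found "using the independent t-test, 85% power, alpha 0.05, and 20% drop-out", also without age or gender.

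**The concern.** Balancing the groups on age and gender removes the contribution of those factors to the variance of the group difference. A between-group test that leaves them out estimates its error from the full spread of outcomes and so puts that contribution back. If age and gender predict the outcome, the estimated standard error is larger than the true one, the test rejects less often than its nominal level, and precision that the design has bought is not used.

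The trial is small, and each planned comparison must reach 0.005, so there is little precision to spare. The omission is more than a detail left to an analysis plan: the article spells out the model terms, the rank tests and the thresholds, and these do not match the allocation it describes.

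**Working it through.** **Inputs**

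- From the article: independent t-test, 85% power, alpha 0.05 (sidedness not stated), 20% drop-out, 78 participants (39 per group), planned threshold 0.005.
- Not in the article: the effect size and SD (only a cited study of the Nine-Hole Peg Test is named), and R2, the share of outcome variance that age and gender explain. R2 of 0.05, 0.1 and 0.2 are assumptions.

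**Step 1: the plan's own figure.** 31 / (1 − 0.20) = 38.75, rounded up to 39 per group, or 78 in total. So 78 corresponds to 31 evaluable per group. The power step cannot be reproduced without an effect size. Solving the noncentral t for 85% power with 31 per group gives d = 0.774 if two-sided, or about 0.69 if one-sided. The two-sided value is used below.

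**Step 2: standard error and type I error.** With full balance on both factors, the ratio of estimated to true standard error is f = 1/√(1 − R2). The true type I error at nominal 5% is 2[1 − Φ(1.96 f)].

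| R2 | f | True type I error |
|---|---|---|
| 0 | 1.000 | 5.0% |
| 0.05 | 1.026 | 4.4% |
| 0.1 | 1.054 | 3.9% |
| 0.2 | 1.118 | 2.8% |

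**Step 3: power for one between-group comparison at one time.** Balance raises the power of the unadjusted test too at alpha 0.05, so the fair comparison is adjusted against unadjusted under the same allocation. Let T be noncentral t with 60 degrees of freedom and noncentrality d·f·√(31/2), and let c be the two-sided critical value (2.000 at 0.05, 2.915 at 0.005). Adjusted power is P(T > c). Unadjusted power is P(T > c·f). The two degrees of freedom spent on the covariates are ignored here.

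| R2 | Alpha 0.05: unadjusted | adjusted | Alpha 0.005: unadjusted | adjusted |
|---|---|---|---|---|
| 0 | 85.0% | 85.0% | 55.5% | 55.5% |
| 0.05 | 85.6% | 86.7% | 55.6% | 58.5% |
| 0.1 | 86.2% | 88.5% | 55.8% | 61.7% |
| 0.2 | 87.6% | 91.8% | 56.1% | 68.7% |

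The gains are about 1, 2 and 4 points at 0.05, and about 3, 6 and 13 points at 0.005.

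**Step 4: simulation at alpha 0.05.** This used 62 evaluable participants, permuted blocks of four within four age-by-gender strata, and 6000 replicates.

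| R2 | Mean SE: unadjusted / adjusted | Type I: unadjusted / adjusted | Power: unadjusted / adjusted |
|---|---|---|---|
| 0 | 0.253 / 0.253 | 4.8% / 4.9% | 85.5% / 85.3% |
| 0.1 | 0.253 / 0.240 | 3.8% / 4.9% | 84.8% / 87.6% |
| 0.2 | 0.253 / 0.226 | 3.2% / 4.9% | 86.8% / 91.0% |

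This agrees with the formulas within simulation error. Adjustment restores the nominal level and costs almost nothing when the factors are not prognostic.

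**Step 5: change within person.** A change contrast was simulated with R2 = 0.2, age and gender effects constant over time, an assumed within-person correlation of 0.7 and an assumed effect of 0.5. The standard error was 0.175 and the power 79.6%, with or without adjustment. Stable age and gender effects cancel within the person.

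**The case against.** The strongest reply is that the hypothesis concerns whether aerobic exercise enhances the response to m-CIMT, and that the group-by-time interaction, the first effect the plan lists, addresses it. That effect is tested against within-person error, and step 5 shows that it loses nothing from stable age and gender effects. This stands. The loss is confined to the group main effect and the between-group comparisons at each time, including every Mann-Whitney test. The plan names all of these, so the point survives in that narrower form.

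A reader might also infer that the plan's error bars are wrong. The documents do not support that for the only confidence interval they name: it is for the pre-post mean difference within each group, which balance between the groups does not make too wide. Nor do they support reading the mismatch as a bias or a false-positive risk, since the error is in the conservative direction.

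Three reservations about size also stand. The article does not say how prognostic age and gender are. The age range of 35 to 80 years makes an effect of age plausible but does not show one. The article does not say how age is matched; if bands are used, continuous age is balanced only in part. Finally, setting adjusted power against the planned 85% would overstate the gain at alpha 0.05, because unadjusted power also rises under balanced allocation.

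**Conclusion.** The mismatch between allocation and analysis is in the text and worth correcting, but it is a matter of efficiency and does not threaten validity. For the group main effect and the per-time between-group comparisons, the tests are conservative to the extent that age and gender are prognostic. The overstatement of the standard error (about 3%, 5% or 12%) and the departure from nominal type I error are upper bounds, because full balance on both factors is assumed.

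The power gain is small at alpha 0.05 and more noticeable at the plan's own 0.005. Those figures rest on assumed R2, a back-solved two-sided effect of about 0.77, 31 evaluable per group and a single-time comparison. They describe the parametric test; no figure was derived for the Mann-Whitney test, where the direction is the same. The interaction test would gain only if age or gender predicts change, which the documents do not show.

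**What to change.** Before the data are examined, prespecify age (continuous) and gender as between-subject covariates in the parametric model. On the non-parametric route, replace the plain Mann-Whitney test with a rank test that is stratified by the allocation factors or adjusted for them as covariates.

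Do not simply add the baseline score as a further covariate. Baseline is already one of the four levels of the time factor and should stay there unless the model is recast as an ANCOVA of the post-baseline values. If it is recast, the relevant R2 is what age and gender explain beyond baseline, so the gain from them may be smaller than shown above.

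The cost is two degrees of freedom and slightly more analysis work. Both variables are known at allocation, so no new data are needed. Stating the adjustment in advance also avoids the charge that covariates were chosen after seeing the results.

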Considering a type of implicit learning, motor priming has been used in neurorehabilitation to facilitate motor learning [22, 26]. The priming theory presumes that when the brain is activated using an intervention delivered prior to the motor learning intervention, it will become more responsive to motor training due to increased neural activity. This “therapeutic window” may result from the modulation of long-term potentiation or long-term depression, such as mechanisms [22, 27, 28]. Movement-based priming, using repetitive or continuous, unilateral or bilateral movements, is an important method of priming the motor cortex in neurorehabilitation [22].

This protocol describes a single-blinded, randomized clinical trial designed to determine whether AE, as a form of movement-based priming, has an effect on the outcomes of m-CIMT, specifically the recovery of the skill of paretic upper limb in persons with chronic stroke. We hypothesize that AE will potentiate m-CIMT, resulting in improved manual dexterity in people in the chronic phase poststroke.

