## Methods

This study is a randomized, single-blinded, intention-to-treat controlled clinical trial in which 78 participants of both genders in a chronic stage poststroke will be randomized into two groups of 39 participants. One group will receive AE combined with m-CIMT, and the other group will perform stretching exercises combined with m-CIMT. The eligibility criteria are presented in Table 1.

**Table 1 Tab1:** Eligibility criteria

Inclusion criteria	
• Stroke resulting in hemiparesis at least six months prior (chronic) • Do not a present lesion in the two hemispheres • Clinical diagnosis of ischemic or hemorrhagic stroke • ≥ 35 and ≤ 80 years old • Participants must present a minimum active movement of 45° of shoulder flexion or abduction, 20° of elbow extension, 10° of wrist extension, 10° of abduction or extension of the thumb, and 10° extension in at least two fingers (metacarpophalangeal and interphalangeal joints) and thumb • Participants must present the ability to pick up a towel using any grip [28] • Participants must present asymmetric of upper extremity, ≤ 2.5 in the Motor Activity Log (MAL) Quantity Scale [10] • Participants must have the ability to remain seated without trunk and arm support for 1 min [29]	
Exclusion criteria	
• Upper limb movement deficits attributable to no stroke pathology	
• Clear signs of dementia or cognitive disorder, indicated in the Mini- Mental State Examination (scores based in years of education, below 13 for illiterate individuals, 18 for individuals with 1 to 7 years of the primary school and 26 for individuals over eight years after primary school) [30, 31] • Individuals with lesion in cerebellar	
• The individuals are smokers, alcohol, or users of illicit drugs at the time of evaluation • Individuals with structural alterations in the cardiovascular and respiratory systems that will contraindicate the aerobic exercise • Individuals with uncorrected auditory and visual deficits • Individuals who present any electrocardiogram alteration or not the cardiorespiratory stress test • Individuals with historical diseases or osteomioarticular alterations • Individuals with body mass index > 28 • Individuals with uncontrolled diabetes mellitus or hypertension, comprehension aphasia, apraxia	

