### Declarations

This study will be conducted following the principles in the Declaration of Helsinki and approved by the Human Research Ethics Committee at the Federal University of São Carlos (Date: February 2018, Study ID#791060170.0000.5504, UFSCar, Brazil). This study is registered in the Brazilian Clinical Trial Registry (RBR-83pwm3). The authors followed the SPIRIT (Standard Protocol Items: Recommendations for Interventional Trials) guidelines for writing clinical trial protocols [30].

During the consent process, the researcher will clarify the objectives and procedures to be used in the research, including details of the methods to be used, the risks and benefits, and stating the possibility of inclusion in either group. The consent also provides a full guarantee of the freedom of the participant to refuse to participate or withdraw their consent at any stage of the research, without any penalty, and shall maintain the confidentiality and privacy of the participants during all phases of the study. All participants will be asked to provide written informed consent prior to enrollment in the study. In the case an individual is unable to sign, an imprint of the thumb will be requested as evidence of consent. All participants will receive a copy of the consent form approved by the ethics committee.

Data and materials from this clinical trial will be made publicly available at the Federal University of São Carlos (UFSCar). The funding sources for this study are FAPESP (Fundação de Amparo à Pesquisa do Estado de São Paulo; grants: 2017/25185–4 and 2017/13655–6). The authors declare they have no competing interests. The author contributions to this protocol and manuscript are as follows: Study design: [name], [name], [name], AB, [name], [name], and [name]. Drafting the manuscript: [name] and [name] Reviewing and editing the manuscript: [name], [name], [name], AB, [name], [name], and [name].

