### Primary outcome measures

#### Self-reported upper limb use

Motor Activity Log (MAL) [35–37] is a structured interview that evaluates the spontaneous use of the more affected upper limb. Each item independently asks about how much and how well the most affected upper limb is used in daily activities over the last week. A 6-point amount of use scale (score range, 0–5) quantifies how much the affected arms are used and a 6-point quality of movement scale (score range, 0–5) quantifies how well the affected arms are used [48]. Scores on this measure have adequate reliability and validity in individuals with stroke [35, 36].

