### Aerobic exercise

Aerobic exercise (AE) will be conducted according to the American Heart Association recommendations and based on cardiopulmonary exercise testing [42, 43]. The AE will be performed on a stationary bicycle. During the AE, blood pressure, heart rate, and the perceived effort on the Borg scale–CR10 [51] will be monitored. Measures will be taken every four minutes during training. The AE will be performed at moderate to high-intensity intervals. The AE protocol will involve 10 min of warm-up in a range of 45% HRreserve, 24 min of interval training, followed by 6 min of cooldown between 45 and 60% HRreserve [65–67]. During interval training, every four minutes, the intensities will be alternated between moderate and high (75–90% HRreserve), and the recovery periods will be in moderate intensity (60% HRreserve). In both groups, individuals will receive standardized verbal feedback every 4 min, “Go on, you’re doing well!”. Individuals who do not reach the target moderate and high intensities of HRreserve during training (75–90%) will be encouraged to maintain at least moderate HRreserve intensity (60%). In addition, if the perceived effort limits target HR frequencies, then the participants will be invited to rest for some minutes and return to training until the total time of the protocol is complete. Participants will have a 10-min rest and then begin the m-CIMT protocol. Hydration will be provided to participants throughout the treatment session.

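### The protocol says participants will not know their arm, but cycling and stretching cannot be hidden from them, so the self-reported Motor Activity Log is an unblinded primary outcome

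*Protocol article*

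**What the plan says.** The design is labelled single-blinded twice, in the Background ("This protocol describes a single-blinded, randomized clinical trial") and at the start of the Methods ("This study is a randomized, single-blinded, intention-to-treat controlled clinical trial"). Neither place says who is blinded.

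Randomization and blinding then makes three claims:

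- Participants: "Participants will not be identified by their real names and will not be aware of which study arm they allocated".
- Assessors: "Thus, the assessors will also be blind, as they will identify the patients by codes and will not have contact with other research procedures".
- Treating staff: "The same standards will be applied to the staff responsible for following the m-CIMT procedures".

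For the data analyst, the same section claims only independence from recruitment, screening, assessment and intervention.

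The Declarations section says that consent covers the objectives, the procedures and details of the methods, as well as "stating the possibility of inclusion in either group". On the experimental arm, the Aerobic exercise section says: "The AE will be performed on a stationary bicycle". The Control therapy section describes 40 minutes of passive muscle stretching.

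Under Primary outcome measures, the first entry is the MAL, which "is a structured interview that evaluates the spontaneous use of the more affected upper limb". Its subheading calls it self-reported. The participant is asked how much and how well the arm was used over the past week. The other primary instruments are the BBT and the NHPT.

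**The concern.** A participant who has been told that there are two groups and what each involves, and who then cycles (or is stretched) before every session, knows which group it is. The participant-blinding sentence therefore states a property that the design does not have.

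This matters most for a primary outcome that consists of the participant's own ratings. Someone who knows that they are in the aerobic priming arm, and who was told the study's objectives, may rate arm use more favourably without any change in the limb. Coding participants and blinding the interviewer cannot prevent this, because the rating originates with the participant. If the sentence stands, a positive MAL result could be reported as a participant-blinded primary finding and given more weight than it can bear.

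The sentence also weakens a safeguard that is achievable. The assessor statement opens with a word that makes it follow from participant unawareness. Its real basis is the coding and the separation of roles named in the same sentence.

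**Working it through.** The main check is textual. The arithmetic at the end is illustrative and changes no figure in the protocol.

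**1. Could participants be unaware of their arm?**

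| Section | What it establishes |
|---|---|
| Declarations | Objectives, methods and the two-group structure are disclosed at consent |
| Aerobic exercise | One arm: 10 min warm-up + 24 min intervals + 6 min cool-down = 40 min on a bicycle |
| Control therapy | Other arm: 40 min of passive stretching, on the floor or seated |
| All of the above | No sham, partial disclosure or concealment of the hypothesis is described |

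Equal contact time and the standardized verbal feedback given in both groups balance attention. They do not disguise which activity is being done. The answer is no.

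**2. Does the label fit?** The section claims blinding of participants and assessors and applies the same standards to m-CIMT staff. That is at least two blinded parties under a single-blinded label. If the participant claim is removed, the label can be read as assessor-blinded, and the inconsistency largely disappears once the blinded roles are named.

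**3. Which primary outcomes are exposed?**

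| Instrument | Source of the score | Safeguard stated |
|---|---|---|
| MAL (amount, quality) | Participant's own rating | None beyond the interviewer's blinding |
| BBT | Count of blocks in 60 s | Blind assessor; scoring confirmed on video |
| NHPT | Time in seconds, maximum 180 s | Blind assessor; scoring confirmed on video |

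MAL is 1 of 3 primary instruments and gives 2 of the 4 primary scores. MAL items are also completed at each m-CIMT session, so participants meet them repeatedly during treatment.

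**4. How large could the effect be?** The documents give no size for expectation bias, so the shift *b* is an assumption. The inputs are:

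- Evaluable per arm: 39 × (1 − 0.20) = 31.2, taken as 31 (Sample size section: 39 per group, 20% drop-out).
- True effect: 0. Reporting shift between arms: *b* = 0.2, 0.3 or 0.5 SD (assumed).
- Test: a single two-sided two-sample t-test, df = 2 × 31 − 2 = 60, non-centrality δ = *b* × √(31/2) = *b* × 3.937.
- P(false significance) = P(|T(df 60, δ)| > t(1 − α/2, df 60)). The critical value is 2.000 at α = 0.05 and 2.915 at α = 0.005. The second level is the per-comparison threshold in Statistical analysis.

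| *b* (SD) | δ | at 0.05 | at 0.005 |
|---|---|---|---|
| 0.2 | 0.787 | 12.1% | 2.1% |
| 0.3 | 1.181 | 21.3% | 4.8% |
| 0.5 | 1.969 | 49.1% | 18.3% |

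With all 39 per arm evaluable, the figures are 14.1%, 25.8% and 58.7% at 0.05, and 2.6%, 6.5% and 25.6% at 0.005. A larger sample does not dilute a bias of this kind; it makes the bias more likely to reach significance.

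**The case against.** The best defence is that the authors meant blinding to the hypothesis, or to which arm is experimental. That would be a legitimate and partly achievable aim. But the text says participants will be unaware of their arm, and consent discloses the objectives. Nothing in the document describes how the hypothesis would be withheld.

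Three further objections have force, and they limit the point.

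- **Mitigation exists.** The control arm receives the same 40 minutes of assisted exercise, and encouragement is standardized across groups. This reduces differences in attention, though it hides nothing.
- **The probabilities are hypothetical.** They follow from assumed shifts and one t-test, whereas the plan is a repeated-measures ANOVA at 0.005 per comparison, with a Mann-Whitney fallback at p < 0.012. They show how the risk scales and demonstrate no bias in this trial.
- **An unblinded self-report may be a primary outcome if declared.** Real-world use of the arm is a target of m-CIMT in this protocol.

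A reader might also infer more than the document supports:

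- That the analyst is claimed to be blind. Only independence is claimed, so a correction should not add analyst blinding.
- That blind assessors perform the video check of the BBT and NHPT. The protocol says that scoring is confirmed on video, not by whom.
- That the dexterity outcomes fall with the participant claim. They are performance tests, and assessor blinding can still protect their scoring. Participant effort and accidental disclosure to an assessor remain possible.

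**Conclusion.** The point holds as a misstatement in the blinding section with a direct consequence for one primary instrument. The claim that participants are unaware of their arm is incompatible with the consent content and with the two visibly different interventions, and it does not fit the single-blinded label. This conclusion rests on the text alone.

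The absence of participant blinding is not itself a fault, since it is not feasible with these interventions. The fault is in claiming it. MAL cannot be protected by blinded assessors, so a between-group MAL difference carries less weight than the current wording implies. The dexterity tests, which match the stated hypothesis, are far less affected.

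The size of any bias is unknown. The range of 2% to 49% for a false MAL finding depends wholly on the assumed shifts of 0.2 to 0.5 SD, 31 evaluable per arm and the choice of threshold. It may be tempting to conclude that MAL must lose its primary status. The documents do not force that; they require only that its unblinded nature be declared.

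**What to change.** Replace the participant-blinding sentence with wording such as:

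> Outcome assessors (and, where feasible, m-CIMT staff) are blinded to allocation. Participants are not blinded to the exercise they receive. The data analyst is independent of recruitment, assessment and intervention.

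Base assessor blinding on the coding and separation of roles, and drop the inference from participant unawareness. Say who is meant wherever single-blinded appears. If blinding to the hypothesis was intended, say so and explain how it is compatible with disclosing the objectives at consent.

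Under Primary outcome measures, add that MAL is an unblinded self-report. State that a between-group MAL difference will be interpreted with that limitation and alongside the assessor-blinded BBT and NHPT, and will not be presented as a blinded result.

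The cost is a few sentences. There is no change to sample size, procedures or data collection.

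Optionally, the sponsor could make the NHPT, the variable used for the sample size, the confirmatory outcome and move MAL to secondary. This defect does not require it. It would cost more than wording, because it alters the primary outcomes of a registered trial, and it should be settled before any outcome data are compared by arm. Rewording the consent description would likewise involve the ethics-approved form and is not needed to resolve the contradiction.
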